##### Quality of Life

QOL will be measured with the WHOQOL-Bref [39]. This 26-item questionnaire is a short version of the WHOQOL-100 and assesses four domains (Physical health, Psychological health, Social relationships, and Environment) as well as one general facet “Overall QOL and General Health”. The questions in the domains are derived from the 24 facets of the WHOQOL-100, with one item from each of the facets. Each item is rated on a five-point rating scale. Higher scores indicate better QOL [39,40]. The WHOQOL-Bref has good psychometric properties as prior research shows that the WHOQOL-Bref is a reliable and valid instrument [40-43].

##### Additional Assessments

Socio-demographic information (ie, sex, age, marital status, and education level) will be obtained from patients at baseline. Clinical information, including date of trauma treatment, ISS, type of trauma mechanism (eg, traffic accident or fall), type of injury (eg, fracture), trauma treatment (eg, operation or medication), consult or treatment from medical psychology (yes/no and which type of treatment), hospital stay (yes/no), in case of hospital stay, admission to intensive care unit, and duration of hospital stay will be abstracted from the patients’ medical records. Possible logistic problems will also be recorded.

### Statistical Analysis

#### Focus Groups

The recorded focus groups are analyzed using open, axial, and selective coding technique [26,27]. Open coding is used to identify different domains: physical, psychological, social, and environmental. Then, axial and selective coding is conducted to determine different themes. These codes consist of single words or short sentences. Two reviewers independently reviewed and coded each of the transcripts and ensured data saturation. Atlas.ti is used for analyzing the transcripts [44]. In addition, patient characteristics, PTSD, anxiety and depressive symptoms, and responses on the questionnaires were analyzed using descriptive statistics in SPSS version 22.

#### Observational Study

The patient characteristic will be studied using descriptive statistics. Then, the baseline characteristics (ie, sociodemographic, clinical, and psychological variables) of participants versus nonparticipants, participants who complete versus drop out during follow-up, and participants who are discharged versus being in the hospital after treatment in the shock room will be compared using independent t-tests and Chi-squared tests. Nonnormal continuous data will be analyzed with Mann-Whitney U tests or Fisher’s exact tests.

Repeated measures of latent class analysis will be used to analyze the courses (ie, time is independent variable) of ASD and PTSD (dependent variables). Moreover, to examine if these different courses of ASD and PTSD (independent variable) could be characterized by socio-demographic (eg, sex, age, education level, and living situation) and clinical (eg, type of trauma, ISS, Glasgow Coma Score, being hospitalized, being treated on the intensive care unit, complications during treatment, and treated by a medical psychologist or psychiatrist), and psychological (eg, anxiety, depressive symptoms, and personality) variables (dependent variables). As a result, each class will represent a different course of ASD and PTSD. By focusing on the characteristics of the different classes, a risk profile will, consequently, be developed to determine which patients are at risk for ASD or PTSD. Sociodemographic and clinical variables are examined as moderating effect, while psychological variables are studied as mediating effects.

Linear mixed models, repeated measures, will be used to examine the effect of ASD (independent variable) on PTSD, anxiety and depressive symptoms, and QOL domains (dependent variables) over time (see Table 2).

The ISS, type of injury and type of trauma mechanism (eg, traffic accident or fall) will be used as covariates. 

**Table 2 table2:** Overview of statistical analysis

Baseline analysis and aims^a^	Independent variables	Dependent variables	Analyses
Patient characteristics	Sociodemographics	N/A^b^	Frequencies Descriptives
	Clinical variables	N/A	Frequencies Descriptives
	Psychological variables	N/A	Frequencies Descriptives
Comparison of patient characteristics	Participants versus nonparticipant	Sociodemographics Clinical variables Psychological variables	Continuous data: Independent t-test, Mann-Whitney U Categorical data: Chi-squared, Fishers’ exact test
	Completers versus noncompleters	Sociodemographics Clinical variables Psychological variables	Continuous data: Independent t-test, Mann-Whitney U Categorical data: Chi-squared, Fishers’ exact test
	Participants being discharged versus being in the hospital	Sociodemographics Clinical variables Psychological variables	Continuous data: Independent t-test, Mann-Whitney U Categorical data: Chi-squared, Fishers’ exact test
Aim 2: Course of ASD and PTSD	Time	ASD^c^ PTSD^d^	Repeated measures, latent class analysis
Aim 3: Risk profile	ASD PTSD	Sociodemographics Clinical variables Psychological	Repeated measures, latent class analysis
Aim 4: Effect of ASD	ASD	PTSD Anxiety Depressive symptoms QOL^e^	Linear Mixed models, repeated measures

^a^The dependent and independent variables for aim 1 could not be provided because this aim focuses on qualitative data.

^b^N/A: Not applicable.

^c^ASD: acute stress disorder.

^d^PTSD: posttraumatic stress disorder.

^e^QOL: quality of life.

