## Introduction

Due to registration and implementation of specialized trauma care, the quality of medical treatment has been improved and survivorship has been increased [1-6]. Trauma is related to physical disabilities (eg, pain, fatigue and impaired wound healing), acute stress disorder (ASD), posttraumatic stress disorder (PTSD), and psychological distress [7-13]. Moreover, trauma patients experience an impaired quality of life (QOL) compared to the general population [14-20].

About 25% of trauma patients have subsyndromal ASD during hospitalization and about 30% had PTSD one month after injury [8,21]. Six months after injury, 49% showed a delayed onset of PTSD. This percentage decreased to 20% at 24 months after injury. A recent systematic review showed that patients diagnosed with ASD had a higher risk of developing PTSD [8]. However, the prevalence rate of patients with ASD who develop PTSD is unknown. Diagnostic criteria for ASD and PTSD are similar; however, dissociative symptoms (eg, depersonalization, derealization, and dissociative amnesia) are only emphasized in ASD and not in PTSD. Moreover, ASD can only be diagnosed within the first month after trauma and last for less than a month, while PTSD symptoms persist for at least one month after injury [22]. PTSD symptoms may begin either after trauma or months or years afterwards [23].

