This multi-method study consists of a focus group study and an observational prospective study. The ultimate goal of this multi-method study is to provide valuable insight into the severity of psychological consequences, including ASD and PTSD, and the need for a psychological intervention study to prevent PTSD. First, focus groups are held to examine patients’ experiences with injury (and their care). In this way, potential factors related to the development of psychological problems (eg, depressive symptoms) and disorders (eg, anxiety, ASD, and PTSD) can be obtained and taken into account for the observational study (aim 1). Subsequently, an aim of the observational study is to examine the courses of ASD and PTSD (aim 2). In addition, it will be examined which socio-demographic (ie, sex, age, marital status, and education level), clinical (ie, type of trauma, Injury Severity Score (ISS), Glasgow Coma Score, being hospitalized, being treated on the intensive care unit, complications during treatment, and treatment by a medical psychologist or psychiatrist), and psychological variables (eg, anxiety, depressive symptoms, and personality) characterize the courses of ASD and PTSD. Subsequently, a risk profile will be developed to determine which patients are at risk for ASD and/or PTSD (aim 3). Finally, to study the effect(s) of the natural course of ASD symptoms on the development of PTSD, anxiety and depressive symptoms, and QOL across time will be analyzed (aim 4).

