#### Observational Study

Data for the observational study will be collected using a structured interview—MINI-plus for ASD and PTSD—as well as self-report questionnaires: (1) the IES-R for ASD and PTSD, (2) HADS, (3) NEO Five-Factor Inventory (NEO-FFI) and the State Trait Anxiety Inventory (STAI) - Trait scale for personality, and (4) World Health Organization Quality of Life assessment instrument-Bref (WHOQOL-Bref) for QOL. All outcome measures will be assessed after treatment in the shock room (baseline), 3, 6, 9, and 12 months after injury. However, ASD and personality will only be measured at baseline (see Table 1).

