**Observational study**				
	MINI-Plus	ASD^e^ PTSD	Primary outcome	Baseline 3 months 6 months 9 months 12 months
	IES-R	ASD PTSD	Primary outcome	Baseline 3 months 6 months 9 months 12 months
	HADS	Anxiety Depressive symptoms	Secondary outcome	Baseline 3 months 6 months 9 months 12 months
	NEO-FFI^f^	Personality	Secondary outcome	Baseline
	STAI^g^-Trait	Personality	Secondary outcome	Baseline
	WHOQOL-Bref^h^	QOL^i^	Secondary outcome	Baseline 3 months 6 months 9 months 12 months

^a^N/A: Not applicable.

^b^IES-R: Impact of Event Scale-Revised.

^c^PTSD: posttraumatic stress disorder.

^d^HADS: Hospital Anxiety and Depression Scale.

^e^ASD: acute stress disorder.

^f^NEO-FFI: NEO Five-Factor Inventory.

^g^STAI: State Trait Anxiety Inventory.

^h^WHOQOL-Bref: World Health Organization Quality of Life assessment instrument-Bref.

^i^QOL: quality of life.

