## Discussion

This is the first multi-method study in trauma patients that examines psychological consequences after injury, using both a qualitative focus group study design as well as an observational prospective design. In the focus group study, the aim was to interview patients about their experiences with the injury, treatment, and rehabilitation. Since it is unknown if and in what way patients’ experiences contribute to the development of psychological problems and disorders. The observational study will examine the course of ASD and PTSD, as ASD after injury is less studied and it is unknown how ASD and PTSD develop over time up to 12 months after injury. Moreover, as a result of all outcome measures, a risk profile of patients may be determined to predict which patients are at risk for developing ASD or PTSD. Altogether, this study will provide information concerning which patients to include in further research that focuses on psychological intervention.

Several factors related to the design and execution must be taken into account. First, response bias may occur in the focus group study. Patients may decline participation because they are not interested in discussing their experiences, or it might be too confronting to talk about their experiences and psychological problems. Second, it is known that the population of trauma patients has a broad variety of trauma mechanisms and injuries. Therefore, it might be difficult to generalize to the whole trauma population. However, concerning the observational study, almost all trauma patients being treated in the shock room will be included from two different Level-1 trauma centers so data saturation can be reached. These centers are located in different provinces and cities in The Netherlands. Therefore, a representative population in the observational study can be included. Third, patients with severe injuries might be less capable to complete the baseline questionnaire almost directly after injury due to being treated at the intensive care unit. Patients will, therefore, be asked to fill in the date of completing the questionnaire and if they needed any help. Then, the time between injury and measurement can be analyzed. This provides information on what time severely injured patients are capable to complete the baseline questionnaire.

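### ASD is measured once, at baseline, so aim 2 cannot model a separate course of ASD over time and the wording of aim 4 promises a course that the data will not contain

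*Protocol article*

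**What the plan says.** Four parts of the protocol article bear on this.

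- **Analysis (Statistical Analysis, Observational Study; Table 2).** "Repeated measures of latent class analysis will be used to analyze the courses (ie, time is independent variable) of ASD and PTSD (dependent variables"). Table 2 repeats this in the row "Aim 2: Course of ASD and PTSD", with time as the independent variable and ASD and PTSD as dependent variables. The text adds that each class stands for a different course of the two disorders and that the risk profile is drawn from the classes.
- **Measurement (Data Collection, Observational Study).** "However, ASD and personality will only be measured at baseline (see Table 1"). Table 1 does not show that restriction. Its MINI-Plus and IES-R rows give ASD and PTSD as a joint domain, with the schedule "Baseline 3 months 6 months 9 months 12 months".
- **Definitions (Introduction).** "ASD can only be diagnosed within the first month after trauma and last for less than a month", whereas "PTSD symptoms persist for at least one month after injury".
- **Aims and rationale.** The Introduction words aim 4 as "to study the effect(s) of the natural course of ASD symptoms on the development of PTSD", among other outcomes. The Discussion motivates the study by saying that "it is unknown how ASD and PTSD develop over time up to 12 months after injury".

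**The concern.** A course needs at least two measurements of the same thing. The Introduction itself explains the term through onset, development and the stability of symptom severity. By the article's own schedule and definition, ASD has one measurement. The ASD part of aim 2 therefore has an analysis that cannot be carried out as written, and the aim 4 wording refers to a quantity that is never observed.

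The risk is that analysts fill the gap by chaining the MINI-Plus ASD diagnosis at baseline to the MINI-Plus PTSD diagnosis at later visits. The first step of that chain mixes a change in the patient with a change in the criteria. Classes that look like recovery or delayed onset could partly reflect the switch. Because aim 3 describes who is at risk by the characteristics of the classes, the problem would pass into the risk profile.

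**Working it through.** The plan states no figure on this point, so there is none to reproduce. The check compares the schedule with the models and then counts parameters.

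**Step 1: occasions per construct**

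| Construct | Usable visits | Basis |
|---|---|---|
| ASD diagnosis | 1 (baseline) | Data Collection text; first-month limit in the Introduction; next visit at 3 months |
| PTSD diagnosis | 4 (3, 6, 9, 12 months) | one-month persistence in the Introduction, with baseline usually taken days after injury |
| IES-R score | 5 (baseline to 12 months) | Table 1; the instrument section presents it as one severity scale for both disorders |

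The PTSD row assumes a baseline shortly after injury. Study Procedures ask for confirmation of consent 1-5 days after the first consent, with the questionnaire after that. The Discussion accepts that some severely injured patients may be later.

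**Step 2: can a latent class model be fitted?**

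With T dichotomous occasions and K classes, the data supply 2^T − 1 independent cell probabilities. The unrestricted model has (K − 1) + K×T parameters.

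| Series | T | Independent probabilities | Parameters, K = 2 | Parameters, K = 3 |
|---|---|---|---|---|
| ASD diagnosis | 1 | 2 − 1 = 1 | 1 + 2 = 3 | 2 + 3 = 5 |
| PTSD diagnosis | 4 | 16 − 1 = 15 | 1 + 8 = 9 | 2 + 12 = 14 |
| IES-R above/below cut-off | 5 | 32 − 1 = 31 | 1 + 10 = 11 | 2 + 15 = 17 |

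For ASD the count fails even with two classes: 1 against 3. For the other two series it is met.

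The count is necessary but not sufficient. I therefore also took the matrix of derivatives of the cell probabilities with respect to the parameters, at 20 random parameter values per model. Its rank equals the number of parameters for PTSD with two classes (9) and for the five-visit series with two or three classes (11 and 17). For PTSD with three classes the rank is 13 against 14 parameters. That unrestricted model is therefore not identified and would need a restriction, such as a smooth trend over time.

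**Step 3: does a combined ASD-to-PTSD series help?**

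On the MINI-Plus it does not. The instrument section refers to separate DSM-5 criteria for the two disorders, and the Introduction says that dissociative symptoms are emphasised only in ASD. By the Introduction's time limits, neither diagnosis can be made both at an early baseline and at 3 months. On the IES-R it does help, in part: the scale is the same at every visit. As described, though, it covers intrusion and avoidance and has a cut-off for probable PTSD only. It gives a course of stress symptoms, not of ASD as a diagnosis.

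**Step 4: aim 4**

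The analysis section and Table 2 enter ASD as the independent variable in a linear mixed model with PTSD, anxiety, depressive symptoms and QOL as repeated outcomes. In schematic form: outcome = b0 + b1×ASD + b2×time + b3×ASD×time + patient effect + error. ASD varies between patients and time varies within them, so b1 and b3 are estimable from a single baseline ASD value. An effect of change in ASD is not.

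**The case against.** The strongest reply is that the article already collects what is needed. The IES-R is a primary outcome at all five visits and is described as measuring both disorders, so the phrase about courses of ASD and PTSD may mean one symptom course on that scale. A condensed article may also leave the choice of instrument for the classes to the analysis plan. This stands as far as it goes. A reader might infer that every curve from ASD to PTSD changes its yardstick; the documents do not support that, because the IES-R series does not.

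A reader might also infer that aims 2 and 4 cannot be estimated at all. That too is unsupported. The PTSD part of aim 2 is estimable, and aim 4 as modelled is a standard analysis; only its wording in the Introduction is at fault.

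Third, the Table 1 conflict may be no more than a merged label, since the text states the restriction plainly. That is fair, but the text cites Table 1 for a restriction that the table does not show.

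What the reply does not remove is that the analysis text and Table 2 name ASD as an outcome that varies with time, while the measurement text gives it one time point. That is stated in the article and is not a matter of missing detail.

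**Conclusion.** The point holds in limited form. ASD is observed at 1 of 5 visits, so a separate course of ASD is not identifiable, and aim 4's reference to a natural course of ASD symptoms has no repeated ASD data behind it. If the classes are built on MINI-Plus diagnoses from baseline onward, the series changes criteria after its first point and the aim 3 risk profile inherits this. The article does not say which instrument defines the classes, so this last consequence is conditional.

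The conclusion rests on the baseline-only statement in Data Collection and the first-month limit in the Introduction. If Table 1 were taken literally instead, ASD would be assessed at visits where the Introduction says it cannot be diagnosed.

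A reader might want to infer how many patients would be misclassified by the switch of criteria. The documents give no basis for such a count. The 25% in the Introduction is subsyndromal ASD during hospitalisation, and the 30% is PTSD at one month, which is not a study visit. Any count would also need an assumption about true change in severity.

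**What to change.** 1. Define the aim 2 latent classes on one consistent measure and name it: either the IES-R score at all five visits, or PTSD diagnosis at 3, 6, 9 and 12 months. Only the first can span baseline. With the second, an unrestricted model on four dichotomous visits supports two classes; three would need a restriction.
2. Remove ASD as a time-dependent outcome from the analysis text and from the aim 2 row of Table 2, and align the wording of aim 2 and the Discussion.
3. Report ASD as a baseline status: its prevalence with a 95% CI, and its relation to the PTSD or stress-symptom classes.
4. Reword aim 4 as the effect of baseline ASD on later PTSD, anxiety, depressive symptoms and QOL. The model itself need not change.
5. Reconcile Table 1 with the Data Collection text, so that the table shows ASD at baseline only.

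The cost is wording in the aims, the analysis section, the Discussion and both tables; no new data are needed. The downside is that the study gives up the claim to describe how ASD develops over 12 months, which its design cannot support. Choosing the IES-R also means that the classes describe symptom severity rather than diagnoses, and the risk profile should say so.

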## Abstract

**Background:**

Injury, medical treatment, and rehabilitation can have major impacts on patients’ wellbeing. About 25-33% of the patients experience an acute stress disorder (ASD) or a posttraumatic stress disorder (PTSD) after injury. ASD is a relatively new diagnosis. Therefore, knowledge about patients’ experiences, the course of ASD and PTSD, and who is at risk for developing ASD or PTSD is lacking.

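### Aim 3 makes patient characteristics the dependent variables and the ASD/PTSD course the independent one, so it describes the classes and does not estimate a patient's joint risk

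*Protocol article*

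**What the plan says.** In the protocol article, Statistical Analysis, Observational Study, latent class analysis first finds the courses of ASD and PTSD. The plan is then "to examine if these different courses of ASD and PTSD (independent variable) could be characterized by socio-demographic", clinical and psychological variables. In that sentence the courses carry the label of independent variable and the characteristics the label of dependent variables. The row "Aim 3: Risk profile" in Table 2 agrees: ASD and PTSD stand in the independent column, and sociodemographic, clinical and psychological variables in the dependent column. The method named in that row is repeated measures latent class analysis.

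The route to the product is one sentence: "By focusing on the characteristics of the different classes, a risk profile will, consequently, be developed to determine which patients are at risk". The Introduction states the same product as aim 3, and the Discussion says that "a risk profile of patients may be determined to predict which patients are at risk for developing ASD or PTSD".

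The paragraph ends by giving the same variables further roles: "Sociodemographic and clinical variables are examined as moderating effect, while psychological variables are studied as mediating effects".

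**The concern.** A risk profile asks: given this patient's age, injury, hospital course and personality, how likely is an adverse course? That is P(course | characteristics). With the roles as written, the analysis answers a different question: among patients in a given course, how are the characteristics distributed? That is P(characteristics | course).

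The two are linked by Bayes' rule, but for several characteristics at once the link needs their joint distribution within each class. The listed variables plausibly overlap: ISS, hospitalisation and intensive care on one side, and anxiety symptoms, neuroticism and trait anxiety on the other. A list of characteristics that are more common in the adverse class does not show which of them add information once the others are known, or what risk a patient with several of them carries.

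At stake is the use that the protocol names for the profile: finding patients who could be offered psychological treatment, and choosing whom to include in later intervention research. Aims 2 and 4 are not touched.

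**Working it through.** The protocol gives no figure for aim 3, so there is none to reproduce. The check has three steps.

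**1. Are the labels a slip?** Table 2, row by row (independent → dependent):

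- Group comparisons: participant, completion or discharge status → characteristics.
- Aim 2: time → ASD, PTSD.
- Aim 3: ASD, PTSD → characteristics.
- Aim 4: ASD → PTSD, anxiety, depressive symptoms, QOL.

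Aims 2 and 4 use the columns in the usual sense. The aim 3 row has the layout of the group-comparison rows, and the running text assigns the same roles. Two places agree, so this is a stated direction and not a typing error.

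**2. What one characteristic can still give.** Assume that it is present in 60% of the adverse class and 30% of the others. With adverse-class share p:

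risk if present = 0.60p / [0.60p + 0.30(1 − p)]

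risk if absent = 0.40p / [0.40p + 0.70(1 − p)]

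- p = 0.15 (assumed): 0.09/0.345 = 26% if present; 0.06/0.655 = 9% if absent.
- p = 0.25: 0.15/0.375 = 40%; 0.10/0.625 = 16%.
- p = 0.33: 0.198/0.399 = 50%; 0.132/0.601 = 22%.

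The last two shares borrow, purely as illustration, the range in the Abstract: "About 25-33% of the patients experience an acute stress disorder (ASD) or a posttraumatic stress disorder (PTSD) after injury". The odds ratio is (0.60/0.40)/(0.30/0.70) = 3.5 in either direction. Since latent class analysis estimates p, risk by one characteristic is recoverable.

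**3. What several characteristics together can give.** Assume k normal characteristics with unit SD in both classes, each with a mean 0.4 SD higher in the adverse class, and every pair correlated ρ within class. Take a patient 1 SD above the other class's mean on all of them. Then

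log odds = ln[p/(1 − p)] + k × 0.4 × (1 − 0.2) / [1 + (k − 1)ρ]

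For k = 10 and p = 0.25: ln(0.25/0.75) = −1.099, and the second term is 3.2/(1 + 9ρ).

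- ρ = 0: −1.099 + 3.200 = 2.101, risk 0.891.
- ρ = 0.3: −1.099 + 0.865 = −0.234, risk 0.442.
- ρ = 0.6: −1.099 + 0.500 = −0.599, risk 0.355.

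All cases:

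| p | k | ρ = 0 | ρ = 0.3 | ρ = 0.6 |
|---|---|---|---|---|
| 0.25 | 2 | 0.387 | 0.353 | 0.332 |
| 0.25 | 5 | 0.623 | 0.408 | 0.348 |
| 0.25 | 10 | 0.891 | 0.442 | 0.355 |
| 0.33 | 2 | 0.483 | 0.446 | 0.424 |
| 0.33 | 5 | 0.709 | 0.505 | 0.441 |
| 0.33 | 10 | 0.924 | 0.539 | 0.448 |

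Within each row, the class-by-class description of every characteristic is identical; only the correlation differs. With two characteristics the ambiguity is small. With five or ten it is large.

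**The case against.** The strongest reply has four parts.

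- **Association is symmetric.** A characteristic over-represented in the adverse class also marks higher risk. In the 15% example, the 60% versus 30% contrast correctly flags a group at 26% against 9%. This stands. A reader might infer that the analysis can give no patient's risk at all, but step 2 shows otherwise.
- **The article does not say that characteristics are handled one at a time.** A reader might infer it from the column labels, yet Table 2 assigns t-tests, Mann-Whitney, chi-squared and Fisher tests only to the three group comparisons. For aim 3 it names latent class analysis and does not say how the characteristics enter. As joint indicators they would yield class probabilities under local independence; as covariates they would give what is needed. This stands as a limit on the concern. But covariates are predictors of class, which is the opposite of the role assigned, and local independence is exactly the kind of further assumption that overlapping variables call into question.
- **The study is exploratory** and speaks of characterising courses; it promises no validated risk score. That lowers the weight. It does not remove the mismatch, because the article also says that the profile is to determine, and in the Discussion to predict, who is at risk.
- **Model-building detail belongs in a fuller document.** Agreed for internal validation, calibration and similar items; their absence from an article is no fault. The direction of the analysis is different, because the article states it, twice.

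The moderator/mediator sentence does not rescue the plan. A variable that is purely an outcome cannot moderate or mediate, so that sentence adds a second inconsistency. Nor does the covariate sentence at the end of the section: it names only ISS, injury type and trauma mechanism.

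**Conclusion.** The point holds in a limited form. As written in the text and in Table 2, aim 3 describes the classes (characteristics given course). It does not estimate the risk of an adverse course given a patient's characteristics jointly, which the risk profile needs. Single-characteristic risks remain recoverable from the class shares; joint risks with correlated characteristics do not, without further assumptions.

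The documents do not support the stronger conclusion that aim 3 is unobtainable from these data, or that univariate testing is planned.

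The size can only be illustrated. For ten characteristics and a 25% class share, the same class profile fits risks from 0.355 to 0.891; for two characteristics, only from 0.332 to 0.387. These figures rest on assumed normality, equal differences of 0.4 SD, equal correlations of 0 to 0.6, and a class share borrowed from the prevalence in the Abstract. The finding about direction rests on none of them.

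**What to change.** In the aim 3 row of Table 2 and the matching sentence in the text, swap the roles: course (class) membership becomes the dependent variable, and the baseline sociodemographic, clinical and psychological characteristics become joint predictors in one multivariable model. Latent class regression or a bias-adjusted three-step multinomial model would do this and carry the uncertainty of class assignment through. For the HADS, which Table 1 schedules at five time points, say that the baseline value is the predictor.

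Reconcile the moderator/mediator sentence with these roles: either drop it for aim 3, or say which effect is moderated or mediated and in which analysis.

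Cost: one table row, one paragraph and a little more analysis work. No new data, visits or patients are needed. The article reports data collection as still under way, so the change could be made before any results.
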